**Definition of serious adverse event**

Serious Adverse Event (SAE) refers to an adverse medical occurrence in subjects, such as death, life threatening, permanent or serious disability or loss of function, hospitalization required or prolonged hospitalization, congenital abnormalities or birth defects, etc., after receiving the investigational product.

- Result in death
- Life-threatening

It means that the subject is already in danger of death when the AE occurs, and it does not mean that the AE may cause death if it becomes more severe.

- Permanent or serious disability or loss of function

AE results may cause serious inconvenience or interference to the normal life and activities of subjects.

- Hospitalization required or hospitalization extended

Due to an AE, the subject has to be hospitalized or his/her hospitalization is prolonged regardless he/she was already to be discharged; It is necessary to clarify that this condition is caused by adverse events, rather than elective operation, non-medical reasons, etc.

- Congenital abnormality or birth defect

The offspring of the subjects suffer from malformations or congenital functional defects.

- Other significant medical events

Medical and scientific judgment is required for deciding whether to accelerate the report of other situations. Significant medical events may not immediately endanger his/her life, cause death or hospitalization, but they are usually considered as a serious event if medical measures are needed to prevent the occurrence of one of the above situations. For example, important treatment in the emergency room or allergic bronchospasm at home, cachexia or convulsion without hospitalization, drug dependence or addiction, etc.

When it fails to clearly judge whether it is a SAE, the investigator should consult with the Sponsor and the Ethics Committee.

**Definition of suspected unexpected serious adverse event (SUSAR)**

Suspected Unexpected Serious Adverse Event (SUSAR) refers to the suspected and unexpected serious adverse events whose nature and severity of clinical manifestations are beyond the existing information such as the investigator's brochure of investigational product, the instructions of marketed drugs or the summary of product characteristics.

**7.3.2. Time period and frequency of collecting information related to adverse events and serious adverse events**

AE collection: This study should start from the signing of the informed consent form by the subject to the time point specified in the study flow diagram. The medical events not related to the study intervention that occur after the signing of the informed consent form and

before the first medication should be recorded in the CRF as medical history/concomitant disease, rather than a part of AEs.

SAE collection: This study should start from the signing of the informed consent form by the subject to the time point specified in the study flow diagram.

The investigator does not have to actively collect AEs or SAEs after the safety follow-up period. However, if the investigator learns of any SAE (including death) at any time after the subject leaves the study and believes that such event is reasonably related to the study intervention or participation in the study, the investigator must collect and report it in a timely manner.

#### **7.3.3. Methods for collecting adverse events and serious adverse events**

Please don't introduce bias when detecting AEs and/or SAEs. Open-ended and non-guided oral questioning of subjects is the preferred method to inquire about the occurrence of AEs, for example:

- "How do you feel?"
- "Has your health improved or deteriorated since the last visit?"
- "Since the last visit, have you taken any new drug? Have you stopped or changed any pharmacotherapy you are using?"

#### **7.3.4. Follow-up visit of adverse events and serious adverse events**

After the initial AE/SAE report, the investigator needs to follow up each subject at the follow-up visit/contact to obtain more information. For all SAEs, and AEs related to the study or causing the subject to stop the study treatment should be followed up until the event is cured (including returning to the baseline value), the subject's status changes to long-term stability, the subject is lost to follow-up or died, or the investigator believes that it's not necessary to continue the follow-up visits or provides other reasonable explanations. The investigator is responsible for conducting or arranging follow-up visits with medical needs or as required by the Sponsor to fully clarify the nature and causal relationship of AEs or SAEs.

When reporting information of follow-up visits, the investigator needs to update the new information with the original electronic report form, and then print the paper report form and

re-sign the name and date. The time limit and process of report of SAE follow-up visits are the same as the initial report.

### **7.3.5. Record and evaluation of adverse events and serious adverse events**

#### **Record of adverse events and serious adverse events**

The investigator is responsible for reviewing all documents related to the event (such as hospital course records, laboratory tests and diagnostic reports) and recording all information related to AEs/SAEs in the case report form. The investigator should try to determine the diagnosis of each event based on physical signs, symptoms and/or other clinical information. If possible, the diagnosis (rather than individual signs/symptoms) should be recorded as an AE/SAE. If the diagnosis is unclear, the named of AE can be temporarily reported by symptoms, signs and abnormal examination, and each symptom, sign and examination shall be recorded separately and updated correspondingly later when the diagnosis is clear.

The investigator, in principle, should not send the copy of medical records of the subject to Jiangsu Simcere Pharmaceutical Group. In some cases, Jiangsu Simcere Pharmaceutical Group may request to provide the copy of medical records of some cases. In this case, the identification information (except the subject code) of all the subjects should be blocked (blackening or other measures) before the copy of the medical record is submitted to Jiangsu Simcere Pharmaceutical Group.

During the collection and evaluation of AEs and SAEs, the name, starting time, ending time or outcome, severity, seriousness, concomitant disease, concomitant medication, event description, causal relationship evaluation, etc. of an AE should be recorded.

#### **Severity of adverse events and serious adverse events**

The severity of all AEs is evaluated using the NCI Common Terminology Criteria for Adverse Events (CTCAE) Version 5.0 in this study. For AEs not defined in the NCI-CTCAE, the following rules will be referred to determine the severity:

|         |                                                                                                            |
|---------|------------------------------------------------------------------------------------------------------------|
| Grade 1 | Mild; asymptomatic or mild symptoms; clinical or diagnostic observations only; intervention not indicated. |
|---------|------------------------------------------------------------------------------------------------------------|

|         |                                                                                                                                                                                                                                                                                               |
|---------|-----------------------------------------------------------------------------------------------------------------------------------------------------------------------------------------------------------------------------------------------------------------------------------------------|
| Grade 2 | Moderate; minimal, local or noninvasive intervention indicated; limiting age-appropriate instrumental activities of daily living, such as preparing meals, shopping for groceries or clothes, using the telephone, managing money, etc.                                                       |
| Grade 3 | Severe or medically significant but not immediately life-threatening; hospitalization or prolongation of hospitalization indicated; disabling; limiting self care ADL (referring to bathing, dressing and undressing, feeding self, using the toilet, taking medications, and not bedridden). |
| Grade 4 | Life-threatening consequences; urgent medical intervention indicated.                                                                                                                                                                                                                         |
| Grade 5 | Death related to an adverse event                                                                                                                                                                                                                                                             |

Severity is the category used to measure the intensity of an event, and both AEs and SAEs can be evaluated using NCI-CTCAE.

#### **Causality assessment of adverse events and serious adverse events**

Causality assessment is one of the criteria used to determine regulatory reporting requirements. The investigator is responsible for assessing the relationship between the study treatment and the occurrence of each AE/SAE. To determine whether the AE is causally related to the drug, the investigator will consult the investigator's brochure or information on the marketed product and consider the following aspects:

- Is there a reasonable temporal relationship between the occurrence of AE and the investigational product? What is the time interval between the onset of AE and the first and last doses?
- Can the symptoms and signs be caused by the mechanism of action of the drug itself or the action of metabolic components?
- Are symptoms/signs relieved or resolved in the absence of other treatments for the AE after dose reduction or discontinuation?
- Do the symptoms/signs reappear or worsen after re-medication?

- Can it be explained by the subject's concomitant diseases, concomitant medications, or other reasons?
- Has similar situation been reported in domestic and foreign literature?

Furthermore, the five-grade method (definitely related, probably related, possibly related, unlikely/remotely related, definitely not related) is used to assess the causality between the reported AE and the investigational product.

The investigator must document and review each AE/SAE, provide causality assessment (although in some cases the investigator may have limited information on the SAE) and update the causality assessment based on follow-up information.

In the assessment of whether the SAE report complies with the standard of accelerated reporting of SUSAR, it is classified as "unlikely/remotely related" in the two-grade method if the causality is assessed to be "not related".

#### **7.3.6. Requirements for regulatory reporting of serious adverse events**

Upon becoming aware of any SAE, whether or not it is related to the investigational product or listed in the investigator's brochure, the investigator should report in accordance with regulatory requirements to meet legal obligations and ethical responsibilities for the safety of subjects and the safety of clinical studies. The investigator should keep the written documents of all the above reports to show that each event received has been properly reported.

The Sponsor will comply with country-specific regulatory requirements for safety reporting to regulatory authorities, the Institutional Review Boards (IRB) / the Ethics Committee (IEC), clinical trial institutions and investigators, and notify local and other regulatory authorities of safety information about the investigational product in accordance with requirements and the Sponsor's policies. The investigator will review the safety reports from the Sponsor that describe SUSAR or other safety-specific information, then archive them with the investigator's brochure and notify the Ethics Committee.

The Sponsor will promptly investigate the SAEs occurred with the investigator, and take necessary actions to ensure the safety and rights of the subjects.

### **7.3.7. Serious adverse event reporting to the Sponsor**

The investigator or designee must complete the rapid SAE reporting within 24 hours of being informed of the occurrence of SAE in the subject, which should include as detailed and useful content as possible. Even if not all the information of the SAE is available at that time, it still needs to be reported within 24 hours. The SAE report should be updated by the investigator within 24 hours after additional relevant information is available.

The investigator or designee will fill in the relevant information using the Jiangsu *Simcere Serious Adverse Event (SAE) Report Form*, print and then sign the date and name, and send the scanned copy to the Sponsor by email ([contact]) within 24 hours.

### **7.3.8. Pregnancy**

All subjects should use reliable contraceptives for 30 days from signing the informed consent form to the last dose to avoid pregnancy of themselves or their female partners. If any pregnancy (including pregnancy confirmed after 90 days) occurs in the subject (or male subject's female partner) within 90 days from the time when the subject receives at least one dose of the investigational product to the last dose, the investigator should examine the safety of the subject and the fetus and take appropriate actions upon discovery; record the pregnancy information in the pregnancy report form and report to the Sponsor within 24 hours after obtaining the information.

All pregnancies should be tracked to outcome until the infant is full term (usually 6 to 8 weeks after the expected date of delivery) or early termination of pregnancy (including spontaneous or selective abortion).

Although pregnancy is not considered an AE or SAE, pregnancy complication or selective termination of pregnancy should be reported as an AE/SAE. Abnormal pregnancy outcomes (e.g., spontaneous abortion, fetal death, stillbirth, congenital anomalies, ectopic pregnancy) are considered SAEs and reported as SAEs (*Simcere Pregnancy Report Form* and *Simcere Serious Adverse Event (SAE) Report Form* are required to be completed at the same time).

In principle, any female subject who becomes pregnant during the study period should immediately discontinue the investigational product.

## 8. Statistical analysis

### 8.1. Determination of sample size

The objective of this study is to evaluate the efficacy and safety of Y-2 Sublingual Tablets in the treatment of acute ischemic stroke. The primary efficacy index is the proportion of subjects with mRS score  $\leq 1$  on Day 90 of treatment. The sample size is calculated based on the primary efficacy index. According to the previous clinical studies, it is expected that the proportion of subjects with mRS score  $\leq 1$  on Day 90 of treatment is 50% in the test group and 40% in the control group. Taking bilateral  $\alpha$  as 0.05, the power as 80% and the random ratio as 1:1, the sample size for each group is calculated to be 388. Considering the 15% dropout rate, then it is planned to enroll 457 cases in each group, with a total sample size of 914 cases.

An interim analysis is scheduled to be performed after approximately 50% of subjects complete the visit on Day 90. The purpose of interim analysis is to reestimate the sample size based on primary efficacy indexes. It is conducted by the Independent Data Monitoring Committee (IDMC) and whether the sample size should be increased or remain unchanged is recommended according to the regulations of the IDMC. The sample size may be increased to 1.5 times the scheduled sample size at most, and won't be reduced.

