### 8.2. Analysis sets

**Full Analysis Set (FAS):** According to the basic principles of intention-to-treatment (ITT), all randomized subjects are included in the full analysis set. The primary efficacy evaluation of this study is based on the full analysis set.

**Per Protocol Set (PPS):** All subjects who have completed the treatment prescribed by the protocol or who have not significantly violated the protocol are included in the per protocol set. The exact definition of a serious protocol deviation will be finalized at the time of data auditing, which may include but is not limited to the following circumstances.

- 1) Serious violation of inclusion criteria that affects the efficacy evaluation;
- 2) Treatment that seriously interferes with efficacy evaluation after inclusion;
- 3) Serious violation of medication regimen, with a total dose intensity of  $< 80$ ;
- 4) Poor compliance that seriously affects the efficacy evaluation;

5) Too long medication delaying during the treatment;

6) Lack of primary efficacy index, etc.

PPS is a secondary analysis set for efficacy evaluation.

**Safety set (SS):** All randomized subjects receiving more than one dose of the investigational product and one safety evaluation are included in the safety set. The safety evaluation of this study is based on the safety set.

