#### **9.3.2. Quality control of the study implemented by the investigator**

- 1) The investigator assumes the duties and functions related to the clinical trial. It should be guaranteed that the investigator has the corresponding qualification, and complete procedures have been established to ensure that the investigator performs the duties and functions related to clinical trials, thus producing reliable data. The consent of the Sponsor should be obtained for authorizing a unit other than the clinical site to undertake study-related duties and functions;
- 2) The investigator should conscientiously implement informed consent, patiently explain to subjects to make them fully understand and cooperate with the study; strengthen health care guidance and monitor subjects' medication compliance;
- 2) Strictly implement the study protocol, do not use the investigational product for other non-investigational purposes, and carefully record the results of various tests, as well as the adverse events or serious adverse events during the study;
- 3) During the implementation of the study, it is best to complete the evaluation of various observation indexes of the same subject by the same investigator to reduce subjective bias;
- 4) After adverse events and/or serious adverse events occur in subjects, the investigator

should actively guide and/or treat the subjects to protect the rights and interests of them;

- 5) The investigator or the person authorized by the investigator (such as the clinical research coordinator) should record the content of the eCRF truthfully, detailedly and carefully according to the requirements for eCRF filling to ensure that the content is true and reliable;
- 6) In view of possible dropout, active actions should be taken to control the dropout rate of cases within 20%.

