### **4.3 Efficacy analysis**

#### **4.3.1 Primary Efficacy Endpoint and Analyses**

The primary efficacy measure in this trial was the proportion of subjects with mRS score  $\leq 1$  at Day 90 of treatment. The main estimated target attributes under the estimated target framework are presented in Section 2.4, and the different coping strategies proposed for the intercurrent events are as follows:

- **Treatment Policy Strategy**

When subjects participating in the trial were successfully randomized and treated, if concomitant medication/therapy was used during the treatment period (see Section 5.8 of the protocol), the investigator did not terminate the treatment or allow them to withdraw prematurely from the study according to the actual situation; or the subject did not withdraw prematurely from the study despite dose delay, interruption, or termination due to an AE; or because of a new coronavirus outbreak, the subject mRS score could only be obtained remotely. For such intercurrent events, the primary efficacy measure will be handled by the treatment policy strategy, i.e., the mRS achievement or failure will be discriminated according to the collected measured mRS score (remote visit mRS score will be considered valid) regardless of whether the intercurrent event occurred.

- **Composite Variable Strategy**

When a randomized subject had no mRS score after starting treatment for any reason; or the subject prematurely withdrew from protocol-specified follow-up because of an AE. Such intercurrent events will be handled for the primary efficacy measure using a composite variable strategy, i.e., the occurrence of such events will be considered as having a mRS score  $> 1$  at the end of follow-up (Day 90 post-treatment).

- **While-on-Treatment Strategy**

When subjects participating in the trial prematurely discontinue treatment or withdraw from the study for reasons other than those mentioned in the above strategy, the on-treatment strategy will be used to deal with the primary efficacy indicators, that is, the mRS score closest to the time of withdrawal will be used as the basis for judging whether the mRS is up to standard.

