#### 4.5.1 Unblinded Sample Size Re-estimation

Sample size re-estimation for interim analysis is performed using promising zone based on conditional power method, setting sample size re-estimation to be performed when 50% of subjects provide primary efficacy indicator data, while limiting the adjusted maximum sample size to only 1.5 times sample size of the initial plan without sample size reduction plan. Meanwhile, it is necessary to ensure that the power of final analysis is maintained at least 80%. According to Mehta CR, Pocock SJ 2011 (Cui L, Hung HM, Wang SJ. Modification of sample size in group sequential clinical trials. *Biometrics* 1999; 55:853--857), to ensure that the Type I error probability ( $\alpha$  level) at the final analysis of the trial is not inflated, the conditional power  $CP(z_1, n_2)$  was calculated based on Equation (1), And divided into three intervals  $CP(z_1, n_2) < 0.41$ ,  $0.41 \leq CP(z_1, n_2) < 0.8$  and  $CP(z_1, n_2) \geq 0.8$  for sample size re-estimation.

$$CP_{(z_1, n_2)} = P(z_2 \geq z_{1-\alpha/2} | z_1) = 1 - \Phi\left(\frac{z_{1-\alpha/2}\sqrt{N} - z_1\sqrt{n_1}}{\sqrt{n_2}} - \frac{z_1\sqrt{n_2}}{\sqrt{n_1}}\right) \quad (1)$$

In equation (1)  $z_1$  represents the  $z$  statistic at the interim analysis and  $z_2$  represents the  $z$  statistic at the final analysis.  $Z_{1-\alpha/2}$  represents the margin corresponding to the  $(1-\alpha/2)$  percentile under the standard normal distribution, where  $\alpha = 0.05$ .  $\Phi(x)$  represents the probability that the observed value  $\leq x$  under the standard normal distribution.  $N$  represents the initial planned sample size,  $n_1$  represents the sample size at the interim analysis,  $n_2$  represents the sample size after the interim analysis in the initial plan, where  $N = n_1 + n_2$ .

Interim analyses of the primary efficacy measure will be performed using the same logistic regression model (see Text Section 4.3.1) as the primary analysis of the primary efficacy measure according to Glenn A. Walker, Jack Shostak 2010 (Mehta CR, Pocock SJ. Statistics in Medicine 2011, 30:3267-3284. Adaptive Increase in Sample Size when Interim Results are Promising: A Practical Guide with Examples), The  $Z$  statistic  $Z_1$  at the interim analysis was calculated from the treatment effect coefficient  $\beta_1$  in the logistic regression model and the corresponding standard error  $SE_{\beta_1}$ , That is  $Z_1 = \beta_1/SE_{\beta_1}$ .

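### The 80% power belongs to 388 completers per arm, not to the full-analysis-set (FAS) primary analysis; and the re-estimation rule cannot keep final power at 80% or more as SAP 4.5.1 says

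*Combined protocol and SAP*

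**What the plan says.** Protocol 8.1 expects that the proportion with mRS ≤1 "on Day 90 of treatment is 50% in the test group and 40% in the control group", takes two-sided alpha "as 0.05, the power as 80% and the random ratio as 1:1", and concludes that "the sample size for each group is calculated to be 388". It then adds: "Considering the 15% dropout rate, then it is planned to enroll 457 cases in each group, with a total sample size of 914 cases". SAP 2.5 repeats the calculation.

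The analysis rules are elsewhere:

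- **Analysis set.** Protocol 8.2 says "all randomized subjects are included in the full analysis set" and bases the primary evaluation on that set. SAP 3 agrees.
- **Dropouts counted as failures.** SAP 4.3.1 applies the composite strategy "When a randomized subject had no mRS score after starting treatment for any reason", and also to withdrawal from follow-up because of an adverse event. Both count as mRS >1.
- **Other dropouts.** Those who stop or withdraw for other reasons are judged on the mRS closest to withdrawal (Protocol 8.4, SAP 4.3.1).

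On the interim, SAP 4.5.1 states that "it is necessary to ensure that the power of final analysis is maintained at least 80" per cent. The same section caps the total at 1.5 times the plan (1370). Table 4-1 allows an increase only when interim conditional power is at least 0.41 and below 0.8.

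**The concern.** Dividing 388 by 0.85 is right when dropouts vanish from the analysis and the completers keep the assumed rates. Here all 457 per arm are analysed, and dropouts enter with an assigned or early outcome. Two effects then work against each other: the denominator is larger than 388, but the difference between arms may be smaller than 10 points. No section gives the power that results.

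The 80% is the figure that justifies the trial's size, and readers may lean on it if the result is not significant. It should describe the analysis that will be reported.

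The sentence in SAP 4.5.1 is a separate problem. It promises a level of power that the cap and the zone limits in the same section do not allow, and this can be shown from the SAP's own equations without any outside assumption.

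**Working it through.** **1. The plan's own figures.** Inputs from Protocol 8.1: 50% vs 40%, two-sided 0.05, 80% power, 1:1.

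n = [1.960·√(2p̄(1−p̄)) + 0.842·√(p₁(1−p₁)+p₂(1−p₂))]² / (p₁−p₂)², with p̄ = 0.45, gives 387.3, so 388. Power at 388 is 80.1%. Then 388/0.85 = 456.5, so 457. All the stated figures reproduce.

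**2. Power of the FAS analysis at 457 per arm (fixed sample).**

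Power = Φ{[(p₁−p₂)·√n − 1.960·√(2p̄(1−p̄))] / √(p₁(1−p₁)+p₂(1−p₂))}.

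All 15% counted as failures: rates 0.85×50% = 42.5% and 0.85×40% = 34.0%. Power = Φ[(0.085×21.38 − 1.960×0.6873)/0.6847] = Φ(0.686) = 75.4%.

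The documents do not say how the 15% divide between the rules, so the other rows are assumptions too:

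| How the 15% behave | FAS rates | Power |
|---|---|---|
| All failures | 42.5% vs 34.0% | 75.4% |
| Same success rate in both arms, 10% to 45% | 44.0% vs 35.5% to 49.25% vs 40.75% | 74.8% to 73.4% |
| Half failures, half early scores at 50% to 100% of the Day 90 rates | 44.4% vs 35.5% to 46.25% vs 37.0% | 78.3% to 81.1% |
| All early scores at 50% to 100% of the Day 90 rates | 46.25% vs 37.0% to 50% vs 40% | 81.1% to 86.1% |
| 50% and 40% already are the all-randomised rates | 50% vs 40% | 86.1% |

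If all dropouts fail, power at other dropout rates is 82.8% (5%), 79.2% (10%) and 71.3% (20%), and it crosses 80% at about 9% dropout.

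**3. Overall power with the re-estimation rule.** This integrates over the interim statistic z₁, using SAP equations (1) and (2), the cap, CHW weights and an unpooled normal approximation.

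| Case | Fixed sample | With rule | Chance of interim CP <0.41 | Chance that the cap binds |
|---|---|---|---|---|
| All failures | 75.6% | 78.4% | 27.3% | 7.9% |
| 50% vs 40% | 86.3% | 88.2% | 18.8% | 6.6% |

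**4. The statement in SAP 4.5.1.** Inputs: N = 914, n₁ = 456 (SAP 4.5), n₂ = 458, cap 1370. CP is conditional power by equation (1).

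At the lower edge, CP = 0.41 means z₁ = 1.271, and (1.960√914 − 1.271√456)/√458 = 1.501. Equation (2) gives n₂* = (456/1.271²)(1.501 + 0.842)² ≈ 1550, so N* ≈ 2006. At the cap the second stage has 1370 − 456 = 914 subjects, and conditional power = 1 − Φ(1.501 − 1.271·√(914/456)) = 1 − Φ(−0.298) = 61.7%.

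| Interim CP | N* without cap | CP at 1370 |
|---|---|---|
| 0.41 | 2006 | 62% |
| 0.45 | 1827 | 66% |
| 0.50 | 1638 | 72% |
| 0.55 | 1478 | 77% |
| 0.588 | about 1370 | 80% |

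The cap stops binding at z₁ ≈ 1.496, CP ≈ 0.588. From there to 0.80 the target is met. Below 0.41 Table 4-1 leaves N at 914.

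**The case against.** The strongest reply is that nothing was miscalculated and that the direction of the gap is unknown. Dividing by 0.85 is common practice. The 50% and 40% come from earlier trials; if those are all-randomised rates, the plan is conservative at 86%. Many dropouts should have a usable score: mRS is taken on Days 14, 30 and 90, subjects who leave are asked for a withdrawal visit, and those who stop drug for an adverse event but stay in the study are scored on their measured mRS. The design also allows an increase, which lifts the all-failure case to 78.4%. All of this stands. It limits what can be said about size, but it does not connect the 80% to the FAS analysis.

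On the re-estimation, the cap is stated in the sentence just before the 80% claim, so no reader is misled about the maximum N. That also stands, but the claim beside it still cannot be met.

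A reader might infer more, in three ways that the documents do not support:

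- **That the true power is 75%.** This needs every dropout to fail, and SAP 4.3.1 does not score all of them that way.
- **That the cap pushes overall power below 80%.** Low conditional power at some interim results is a different quantity, and overall power at 50% vs 40% is 88%. The no-increase zone is also about three times as likely as the capped zone.
- **That Protocol 9.3.2 contradicts the 15%.** It says "active actions should be taken to control the dropout rate of cases within 20" per cent. That is an operational ceiling, which can sit beside a lower planning rate.

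Finally, the consequence is modest. The IDMC kept N at 914, and its third minutes record follow-up as finished and agree to database lock. Restating power changes no estimate, interval or type I error.

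**Conclusion.** Wrong as written, in wording only. The 80% is correct for 388 completers per arm at 50% vs 40%, and it is not the power of the specified primary analysis. At the plan's 15% dropout, fixed-sample FAS power is about 73% to 86%: 73–75% if dropouts show no treatment difference, 75.4% if all fail, 78–81% in the half-and-half case, and 86.1% if the assumed rates already cover everyone randomised. With the re-estimation rule the all-failure case is about 78%, and 50% vs 40% about 88%. Where the trial falls in this range depends on a split, and on the meaning of the assumed rates, that the documents do not give. They do not support calling the trial underpowered.

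The SAP 4.5.1 point rests only on its own equations: the 80% target is met for interim conditional power of about 0.59 to 0.80 and missed from 0.41 to 0.588, and below 0.41 the rule does nothing. As N stayed at 914, this concerns the accuracy of the plan's text.

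**What to change.** Two wording changes, with no added patients and no change to the analysis.

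1. **Protocol 8.1 and SAP 2.5.** Add: *The 80% power is for 388 completers per group. In the FAS with 457 per group, fixed-sample power at 15% dropout is about 75% if all dropouts count as failures (83% at 5%, 79% at 10%, 71% at 20% dropout, same assumption) and up to 86% if 50% and 40% are the rates in all randomised subjects.*
2. **SAP 4.5.1.** Replace the statement that power is kept at 80% or more with: *The re-estimation targets 80% conditional power where the 1.5-fold cap does not bind (interim conditional power about 0.59 to 0.80). For interim conditional power 0.41 to 0.59, conditional power after the increase is 62–80%. Below 0.41 the sample size is not changed.*

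Protocol 9.3.2 needs no change. The cost is a few sentences and a stated power that becomes a range with its assumption.
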